### Sample size determination, randomization, and statistical analysis

Individual randomization of physicians within a group-practice and individual patients to either the control or intervention arm of the study is not feasible [32]. A cluster randomized design was chosen in which family physicians within a group practice were randomized to the same experimental group (control or intervention) and considered a cluster. Randomization of clusters will be conducted by a biostatistician using a computer-generated list and all of a physician’s patients will receive the same experimental treatment (control or intervention). Our protocol defines a multi-level analysis facilitating analysis of the intraclass correlation coefficient (ICC) for each primary group-level outcome (patients, FP, clinics/clusters) [32]. To ensure an even distribution of cluster-level characteristics between experimental groups, clusters will be randomized within strata based on membership in the Physician Integrated Network (PIN) and/or Uniting Primary Care Oncology Network (UPCON) [28]. These represent two quality improvement initiatives in Manitoba (Table 2). Clusters will be block randomized based on the number of collaborating FPs within a practice. An absolute increase in FOBT screening rates of 15% from the current 42% in Manitoba will be considered clinically significant [14]. Sample size was determined by a biostatistician using PASS (Power and Sample Size, 2002) software and a computer simulated ICC value of 0.6 [33] taking into consideration the clustered design of the trial [34]. This is a very conservative estimate of the minimum detectable effect size (MDEF) given the proposed sample size. Based on logistic regression a cluster size of 41 clusters each enrolling 30 to 35 patients (of which 80% are in the group that does not utilize the supplied intervention/magnet and 20% are in the group that does utilize the intervention/magnet; 1230 observations) will achieve 90% power at a 0.05 significance level to detect a change from the baseline value of 0.400 to 0.550 and corresponds to an odds ratio of 1.833. In the event that family physician collaboration/retention and/or patient recruitment proves to be more difficult than anticipated, a logistic regression with a cluster size of 28 (840 observations) achieves 80% power with the same outcomes.

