Research has shown a majority of patients completing the FOBT do so within 4 to 6 weeks [20]. In order to allow adequate time to complete the FOBT and return it to the laboratory, patients will be given four months to do so. Those patients not returning their FOBT test within a period of four months will be scored as failing to complete the FOBT test.

Analysis of results will be based on the intention to treat (ITT) model. All Statistical analysis will be performed using SAS 9.2 ® software. Categorical variables will be compared using the Chi-square test. The time taken to return FOBT cards will be analyzed with Cox’ Proportional Hazards Regression analysis. Due to the clustered design, study outcomes will be measured at the level of the patient, family physician, and medical clinic/cluster. The analysis will utilize multi-level logistic regression that accounts for variance among patients with the same FP, FP within the same cluster, and among the clusters. The SAS® GLIMMIX procedure will be used to model patient FOBT completion rate (response variable). This will enable evaluation of the rate of patient FOBT compliance within medical clusters and individual FPs. Sources of variance included in the model will include cluster level (treatment, electronic medical record or paper charts, PIN and/or UPCON membership), family physician level (gender, solo/group practice), and patient level (age, gender, socioeconomic status, and previous FOBT screening history) variables as well as random variation.

A computerized randomization number list will be used to select 10 patients per FP to be contacted for a Post-Study Follow-Up Survey (Additional files 4 and 5) conducted by telephone. Only those patients providing permission to be contacted will be included. Those patients surveyed will be asked for permission to document their Personal Health Identification Number which will facilitate future studies conditional to Health Research Ethics Board (HREB) approval of analysis of repeat colorectal cancer screening behavior over time.

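### The Cox regression for time to FOBT return and the chi-square tests carry no stated allowance for clustering, so comparisons by arm or other cluster-level factors would be anti-conservative

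*Protocol article*

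**What the plan says.** All of this is in the protocol article, Methods/design, under *Sample size determination, randomization, and statistical analysis*.

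- Unit of randomization: "family physicians within a group practice were randomized to the same experimental group (control or intervention) and considered a cluster".
- Categorical data and time to return of the FOBT card: "Categorical variables will be compared using the Chi-square test. The time taken to return FOBT cards will be analyzed with Cox" regression. The variables and groupings for the chi-square tests are not listed. The text then moves on to levels of measurement: "Proportional Hazards Regression analysis. Due to the clustered design, study outcomes will be measured at the level of the patient", followed by the physician and the clinic or cluster.
- Allowance for clustering: "The analysis will utilize multi-level logistic regression that accounts for variance among patients with the same FP", for physicians within a cluster, and among clusters. Its response is stated: "GLIMMIX procedure will be used to model patient FOBT completion rate (response variable").

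Under *Setting and participants* the article adds that the effect of the kit distribution method on uptake will be assessed. That method is not among the covariates listed for the GLIMMIX model.

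**The concern.** Three methods are named, and one of them allows for clustering. A chi-square test or a Cox model with its default variance treats patients as independent. Here everyone in a practice has the same arm, and patients also share a physician. For a factor fixed at practice level, positive within-practice correlation makes the true variance of the comparison larger than the default variance.

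Three sets of results are exposed:

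- **The Cox comparison of arms.** Its events are the same FOBT returns that make up the primary outcome. A paper could show a significant arm effect on time to return beside a multi-level completion result that is not significant, purely because of the variance used.
- **Kit distribution method.** The article describes it as part of each physician's current practice, so it is likely to be clustered much as arm is. With no place in the listed mixed model, it falls to the chi-square test by default.
- **Arm comparisons of categorical items** from the in-clinic and follow-up surveys.

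**Working it through.** The article gives no figure for the error rate of these tests, so there is none to reproduce. The check computes the consequence of following the text.

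**Inputs**

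- Abstract: 36 clusters, 76 physicians, 30 patients each. Patients per cluster: 76 × 30 / 36 = 2280 / 36 = 63.3.
- Sample size text: "a cluster size of 41 clusters each enrolling 30 to 35 patients", with 1230 observations, so 1230 / 41 = 30 per cluster.
- Follow-up survey: 10 patients per physician, so at most 76 × 10 / 36 = 21.1 per cluster.
- ICC: no value is given for time to return or for categorical items. The values 0.01, 0.02 and 0.05 are my assumptions, shown as a range.

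**Formulas**, for a factor that is constant within clusters, with m patients per cluster

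- Design effect: DE = 1 + (m − 1) × ICC.
- Correct standard error / naive standard error = √DE.
- Actual error of a nominal two-sided 5% test = 2 × (1 − Φ(1.96 / √DE)).

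Example with m = 63.3 and ICC 0.05: DE = 1 + 62.3 × 0.05 = 4.12; √DE = 2.03; 1.96 / 2.03 = 0.966; error = 2 × (1 − Φ(0.966)) = 33%.

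| Patients per cluster | Assumed ICC | DE | √DE | Actual error |
|---|---|---|---|---|
| 63.3 | 0.01 | 1.62 | 1.27 | 12% |
| 63.3 | 0.02 | 2.25 | 1.50 | 19% |
| 63.3 | 0.05 | 4.12 | 2.03 | 33% |
| 30 | 0.01 | 1.29 | 1.14 | 8% |
| 30 | 0.02 | 1.58 | 1.26 | 12% |
| 30 | 0.05 | 2.45 | 1.57 | 21% |
| 21.1 | 0.01 | 1.20 | 1.10 | 7% |
| 21.1 | 0.02 | 1.40 | 1.18 | 10% |
| 21.1 | 0.05 | 2.01 | 1.42 | 17% |

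**Simulation check.** There was no treatment effect, 36 practices with 76 physicians and 30 patients each, 42% completion, practice-level beta-binomial clustering, and 2000 runs per ICC. Rejection rates at nominal 5% for the naive chi-square test and the naive Cox score (log-rank) test were:

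- almost no clustering (ICC 0.0001): 5% and 5%
- ICC 0.01: 12% and 13%
- ICC 0.05: 31% and 32%

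The formula is therefore adequate for both methods, and the Cox analysis behaves like the chi-square test.

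**The article's own ICC.** The sample size uses 0.6. If that value applied to these outcomes, DE would be 1 + 29 × 0.6 = 18.4 at 30 per cluster and 1 + 62.3 × 0.6 = 38.4 at 63.3. The standard error ratios would be 4.3 and 6.2, and the actual error about 65% and 75%.

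**The case against.** The best case for the plan is that a variance estimator for a supporting analysis is a detail that an article may leave to a fuller document. The text never calls the Cox model or the chi-square test unadjusted, and a Cox model with robust variance is still Cox regression. The authors plainly recognised clustering: they announce multi-level analysis in the abstract, and the sentence after the Cox sentence begins from the clustered design. Time to return is not listed under *Primary outcome* or *Secondary outcomes*.

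Part of this stands. No deliberate assumption of independence can be inferred, and the Cox analysis is a supporting one. But the article is not silent on method. It names three analyses and gives a cluster allowance to one, with one stated response. A logistic model cannot supply the variance for a Cox model, and nothing extends it to the chi-square tests. The sentence on levels concerns measurement and names no frailty term, robust variance or adjusted test.

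The scope also has limits:

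- Use of the telephone line and website exists only in the intervention arm, so describing it involves no arm comparison.
- Comparisons on factors that vary within practices, such as patient gender, need not be anti-conservative.
- Follow-up survey items have about 21 patients per cluster, not 63, so their inflation is smaller.

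**Conclusion.** The point holds for three things: the Cox comparison of arms, chi-square tests by arm, and chi-square tests by other practice- or physician-level factors. Under the assumed ICCs of 0.01 to 0.05, the actual error of a nominal 5% test is about 12% to 33% at 63 patients per cluster, 8% to 21% at 30, and 7% to 17% for follow-up survey items. These figures assume roughly equal cluster sizes and a factor that is constant within clusters. For kit distribution method they are approximate, because it is recorded patient by patient and may vary within a practice.

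A reader might infer two stronger claims that the article does not support:

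- **That the primary result is compromised.** It is not. FOBT completion is to be modelled with variance among patients, physicians and clusters.
- **That the intervals will be far too narrow in any event, with an error near 75%.** That figure needs an ICC of 0.6 for these outcomes. The 0.6 is a simulated value adopted for the completion sample size and described there as very conservative. Nothing ties it to survey answers or hazards. At an ICC of 0.01 with 30 patients per cluster, the error is only about 8%.

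The plan should be corrected, but the trial's main conclusion does not depend on it.

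**What to change.** Add a sentence to the analysis section stating that every comparison by arm, or by another cluster- or physician-level factor, will account for clustering:

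- **Time to FOBT return:** Cox model with cluster-robust variance at the level of the randomized cluster (PROC PHREG with COVS(AGGREGATE) and the cluster as ID), or a shared-frailty model at that level.
- **Categorical comparisons:** Rao-Scott chi-square (PROC SURVEYFREQ with a CLUSTER statement), or a mixed model with random cluster and physician effects. The mixed model suits kit distribution method, which could be added to the planned GLIMMIX model.

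Comparisons on factors that vary within practices and descriptions of aid use within the intervention arm can stay as they are for this purpose. The change needs no further patients or data. It costs a few lines of SAS and gives wider confidence intervals for the affected comparisons.

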### Creating collaborative partnerships between community-based family physicians and primary healthcare researchers

The first step in creating the collaborative partnerships with Winnipeg family physicians will involve composing a list of medical clinics and community-based family physicians within the outlined community areas. Once defined, the study coordinator (KC) will make randomized cold-calls to each medical clinic to inform them of the study and delivery of the primary care provider (PCP) recruitment letter*.* The PCP recruitment letter briefly outlines the proposed research study, provides information on a small honorarium to acknowledge the efforts of the FP/clinics ($500.00 for 1 to 2 FPs; $1000.00 for 3 to 5 FPs; $1,500.00 for 6–9 FPs; and $2,000.00 for ≥10 FPs) and inquires about interest in collaborating on the study. Meetings will be arranged with interested FPs/clinics to outline the study in more detail and to determine collaboration. All methods used establish collaborative partnerships with FPs will be documented in an attempt to establish insights into those strategies that best support these efforts.

### Experimental treatment group

All FPs will follow their usual clinical practice for CRC screening with the FOBT during the patient periodic health examination. FPs in the intervention group will provide patients with access to the study specific colorectal cancer information and screening nurse-managed telephone support line and website by giving them a refrigerator magnet with the telephone number and website URL (Figure 2). Access to the telephone support line and/or website is patient initiated. All patients in both treatment groups will be assigned a study-specific, seven character, alpha-numeric identification number. For patients allocated to the intervention group, each patient’s magnet will be assigned the same study-specific identification number which will be used by patients in the experimental group to access the telephone and website patient aids, facilitate tracking patient use of the intervention support tools, and protect personal health information.

**Figure 2 F2:**
[figure not shown]
**Study magnet design. **Family physicians randomized to the intervention treatment group will provide each of their patients with a study refrigerator magnet (shown above) containing a unique seven character alpha-numeric study identification number that (1) facilitates access to the patient decision aids (a nurse-managed telephone support line and a website), (2) is linked to the Patient Tracking Form used by the family physician during the periodic health examination, and (3) linked to In-Clinic Patient Survey (Additional file 6). Family physicians will enroll between 30 to 35 patients who have provided their consent to participate in the study. The magnet was designed by the CIHR/CCMB Primary Care Oncology Research Team.

### The colorectal cancer information and screening telephone support line and website

The scientific literature and credible health resources [1,3,8,9,11-13] will be used to gather patient relevant colorectal cancer and screening information. Patient health education files will be generated based on this information to address patient’s most common questions and issues related to FOBT screening [3,8-10]. A survey conducted in Manitoba [3] and personal communications between the study coordinator (KC), family physicians and their support staff, and lab technicians will also inform the development of the patient decision aids. Website resource development was based on the same information in addition to feedback from CRC patients/survivors (n = 4), two small groups (n = 5–8) of average risk men and women, and the PCO-NET group during three quarterly workshops.

Each patient will provide the registered nurse taking the call with their personal seven digit alphanumeric study identification number. Similarly, patients logging on to the website will be guided to enter their study identification number and create a personal password that allows them access to the site. Patients initiating a call to the telephone line will be able to ask questions which will be answered by a registered nurse using the health education files. If a patient asks a question to which there is no health education file/answer, the question will be documented by the registered nurse and the patient given the contact information of the study coordinator and/or provided the website address. Patients logging on to the website are able to view each webpage according to their specific questions and areas of interest (Figure 3 for website site map). Each page visited by each patient will be recorded. Patients will be able to email the study coordinator if they have further questions/comments. We will be able to track the number of calls made by each patient, the health education files accessed by each patient, the number of times they access the website and the website content/pages they visit, as well as any additional questions asked that were not contained in the health education files or website. Patient study identification number will correspond to the study identification number on the Patient Tracking Form which facilitates linking patient demographic information, FOBT completion status, and In-Clinic and Follow-Up Survey data with telephone and website usage.

**Figure 3 F3:**
[figure not shown]
**Site Map for the colorectal cancer information and screening study website. **To obtain a website identification number and password to access to the study website, please contact [name] ([contact]).

### Description of the study protocol

This study protocol was approved by The University of Manitoba Health Research Ethics Board (Additional files 7, 8, 9 and 10) and is outlined in detail in Figures 4, 5, 6 and Tables 3–4. Table 5 provides an outline of and link to the study protocol forms and surveys along with a summary of the information obtained from each and the anticipated number of responses. Table 6 provides a description of the contents of the study set-up package. Upon arrival for their periodic health examination, eligible patients (Table 2) in both study groups will be asked by medical clinic support staff to complete the In-Clinic Patient Survey. This survey provides an explanation of the study and asks the patient to respond to a few general questions related to colorectal cancer screening, computer use for health-related questions, and permission to be contacted for the follow-up survey. It will function as the patient consent form. A business card will be attached to each In-Clinic Patient Survey providing the telephone numbers for the University of Manitoba Health Research Ethics Board and the Study Coordinator to facilitate patient contact as necessary. Patients declining to answer the survey return it to the clinic support staff who document that the patient declined to participate. Those patients completing the In-Clinic Survey will bring it with them and gave it to their FP during their periodic health examination. The FP will determined patient eligibility. All FPs conduct CRC screening as per their standard clinical practice. If a patient is ineligible, the FP will not enroll the patient. If the patient is eligible, the FP will enroll the patient by filling out a Patient Tracking Form. FPs will have a Patient Tracking Form Binder containing a Patient Tracking Form for each eligible patient in each of their evaluation rooms. Each Patient Tracking Form will have a removable sticker with the unique study identification number on it. The FP will remove and affixed this sticker to the patient’s In-Clinic Survey. Patients will be given four months to complete their FOBT. FPs in the intervention group will provide each eligible patient with a refrigerator magnet (paper clipped to the corresponding Patient Tracking Form). The protocol design allows us to determine how many patients provided with the magnet called the telephone support line as well as the number of times they called and their most common questions. It also allows us to determine which patients accessed the website, the pages they visited, and the information they were most interested in. Approximately four months after the last patient is enrolled, each FP will be provided with a list of their enrolled patients on which they will document the date of FOBT completion for those patients completing the test or an incomplete (for those not completing the FOBT). Patient FOBT results will not be collected. Using a computer generated randomization list, 10 patients per FP who agreed to be contacted for the Post-Study Follow-Up Survey will be contacted via telephone to complete the survey.

**Figure 4 F4:**
[figure not shown]
**Flow Diagram of study protocol for family physicians. **Ψ, strata based on membership in the Physician Integrated Network (PIN) and/or Uniting Primary Care and Oncology Network (UPCON); blocked based on the number of family physicians per cluster.

**Figure 5 F5:**
[figure not shown]
**Flow diagram of control group Study Protocol for family physicians and support staff.** * Family Physicians will complete the Family Physician Survey (Additional file 11) upon completion of study requirements. Please refer to text for further details.

**Figure 6 F6:**
[figure not shown]
**Flow diagram of intervention group study protocol for family physicians and support staff. *** Family Physicians will complete the Family Physician Survey upon completion of study requirements. Please refer to text for further details.

**Table 3 T3:** Study protocol steps for control group

**Study protocol step**	**Description/details of study protocol step**
**STEP #1**	Patients between the ages 50–74 report to the reception desk/support staff for their Periodic Health Examination (PHE) or regular visit in which the family physician determines there is an opportunity for colorectal cancer screening (Fecal Occult Blood Test; FOBT).
**STEP #2**	Support staff provide patients meeting the above criteria with the In-Clinic Patient Survey (found in the study binder marked In-Clinic Patient Surveys) on a clipboard.
**STEP #3**	Patient decides whether they will fill out the In-Clinic Survey.
	If a patient declines to fill out the In-Clinic Survey, the support staff documents the patient’s age, gender, and reason(s) they declined to fill out survey (on the back of the In-Clinic Survey). Please clip the survey to the front of the study binder marked In-Clinic Patient Surveys.
	If a patient fills out the survey, they take it with them and give it to their family physician at the beginning of their appointment. The clipboard is returned to support staff so they are able to use it for the next patient.
**STEP #4**	The patient gives their In-Clinic Patient Survey to their family physician at the beginning of their appointment.
**STEP #5**	The family physician takes the In-Clinic Survey from the patient and determines if they are eligible for the study based on the inclusion/exclusion criteria found at the front of the family physicians study binder marked Patient Tracking Forms.
	If patients are ineligible, clip the In-Clinic Survey to the front of study binder marked Patient Tracking Forms.
	If patients are eligible:
	Turn to an unused Patient Tracking Form in the study binder. Record the date, the patient’s NAME, and mark the checkbox indicating the method of FOBT distribution to the patient.
	Remove the study ID number sticker from the Patient Tracking Form and place it on the patient’s In-Clinic Survey.
	Clip the In-Clinic Survey to the front of the Study Binder.
	Proceed with colorectal cancer screening with the Fecal Occult Blood Test (FOBT) as per usual clinical practice.
**STEP#6**	Study coordinator ([name]) will arrange a convenient date to collect forms and determine those completing their FOBT. In the event that you require more In-Clinic Surveys or have a question/comment/concern, please contact [name] at [name] or [contact]

**Table 4 T4:** Study protocol steps for intervention group

**Study protocol step**	**Description/details of study protocol step**
**STEP #1**	Patients between the ages 50–74 report to the reception desk/support staff for their Periodic Health Examination (PHE) or regular visit in which the family physician determines there is an opportunity for colorectal cancer screening (Fecal Occult Blood Test; FOBT).
**STEP #2**	Support staff provides patients meeting the above criteria with the In-Clinic Patient Survey (found in the study binder marked In-Clinic Patient Surveys) on a clipboard.
**STEP #3**	Patient decides whether they will fill out the In-Clinic Survey.
	**If **a patient declines to fill out the In-Clinic Survey, the support staff documents the patient’s age, gender, and reason(s) they declined to fill out survey (on the back of the In-Clinic Survey). Please clip the survey to the front of the study binder marked In-Clinic Patient Surveys.
	**If **a patient fills out the survey, they take it with them and give it to their family physician at the beginning of their appointment. Clipboard is returned to support staff so they are able to use it for the next patient.
**STEP #4**	The patient gives their In-Clinic Patient Survey to their family physician at the beginning of their appointment.
**STEP #5**	The family physician takes the In-Clinic Survey from the patient and determines if they are eligible for the study based on the **inclusion/exclusion criteria found at the front of the family physicians study binder marked Patient Tracking Forms.**
	If patients are **ineligible**, clip the survey to the front of Study Binder
	If patients are **eligible**:
	Turn to an unused Patient Tracking Form in the Study Binder and record the **date,** the **patient’s NAME,** and mark the **checkbox** indicating the method of FOBT distribution to the patient.
	Remove the study ID number sticker from the Patient Tracking Form and place it on the In-Clinic Survey.Remove study magnet from Patient Tracking Form and give it to the patient. Clip the In-Clinic Survey to the front of the Study Binder.
	Proceed with colorectal cancer screening with the Fecal Occult Blood Test (FOBT) as per usual clinical practice.
**STEP#6**	Study coordinator ([name]) will arrange a convenient date to collect forms and determine those completing their FOBT. In the event that you require more In-Clinic Surveys or have a question/comment/concern, please contact [name] at [name] or **[contact]**

**Table 5 T5:** Outline of study protocol forms and surveys and anticipated number of responses

**Study protocol form/survey**	**Individual completing form/survey**	**Information obtained**	**Anticipated number of responses**
Clinic Characterization Form^1^	Medical Cluster and Family Physician	Standard FOBT practice; Electronic medical record; on-site lab; solo/group practice	50 to 80
Family Physician Survey^2^	Family Physician	Experience with study protocol and value to clinical practice; facilitators and barriers to study collaboration; interest in future community-based primary healthcare research projects	50 to 80
FOBT Completion Status Form	Family Physician	Patient FOBT status four months post requisition)	50 to 80
Patient Tracking Form^3^	Family Physician	Date of FOBT requisition; Patient name; FOBT kit distribution method	1,500 to 2,400
In-Clinic Patient Survey^4^	Patient	Age, gender, postal code, Previous FOBT screening history, internet use for health related questions; exposure to advertisements related to FOBT screening; consent for Post-Study Follow-Up Survey	1,500 to 2,400
Post Study Follow-Up Survey (control)^5^	Patient (10 patients per family physician)	Colorectal cancer screening and FOBT experience with family physician; FOBT test instructions; computer access frequency of use; facilitators and barriers to completing the FOBT; Personal Health Information Number	250 to 400
Post Study Follow-Up Survey (intervention)^6^	Patient (10 patients per family physician)	Colorectal cancer screening and FOBT experience with family physician; FOBT test instructions; computer access frequency of use; facilitators and barriers to completing the FOBT; experience with and usefulness of patient decision aids (telephone-support line and website); Personal Health Information Number	250 to 400

^**1, 2, 3, 4, 5, 6**^ Additional files 2, 11, 3, 6, 4 and 5 for each form and survey.

**Table 6 T6:** Description of study set-up package

**Study package delivered to each collaborating family physician**	**Description/details**
**In-Clinic Patient Survey Binder(s):**	Contents:
● thank you page for support staff	● In-Clinic Patient Surveys for support staff
● step-by-step outline of the study protocol,	● business card attached to each survey providing contact information for the study coordinator and the University of Manitoba Health Research Ethics Board (attached to clipboards and replaced when necessary)
● step-by-step flow diagram of the study protocol	
● patient eligibility criteria	
● contact information for the study coordinator	
**Clipboards with pens**	Two clipboards and pens per family physician
**Patient Tracking Form Binders:**	● Each family physician is provided with one Patient Tracking Form Binder per evaluation room (usually two)
● step-by-step outline of the study protocol	● the 30–35 Patient Tracking Forms are split between the these binders
● step-by-step flow diagram of the study protocol	
● patient eligibility criteria	● Each Patient Tracking Form corresponds to a specific patient with corresponding seven-digit alphanumeric study identification number
● contact information for the study coordinator	● family physician records the date of FOBT requisition, patient’s name, FOBT distribution method, removes the sticker from the form and attaches it to the corresponding patient’s In-Clinic Survey

The study coordinator will conduct site visits at regular intervals (approximately every two to three weeks) to facilitate regular communication, answer questions, and address issues with family physicians/support staff/medical clinics, build rapport and trust with partners, ensure successful study protocol implementation, and to pick up In-Clinic Surveys and Patient Tracking Forms.

